### Statistical analysis

The primary outcome is the proportion of postoperative infections within 48 h postoperatively. Fisher’s exact test will applied to compare the proportions between mannitol + low-dose amikacin arm vs full-dose amikacin arm and mannitol + low-dose amikacin arm vs ceftriaxone arm, respectively. To account for multiple comparisons, single-step method will be applied to control the family-wise error rate. Odds ratios with 95% confidence intervals and associated *p* value will be reported. Due to its exploratory nature and limited number of participants, no interim analysis will be performed. Microbiological eradication will be compared between the same groups mentioned in the primary analysis using *t*-tests. Difference in means with 95% confidence intervals and *p* values will be reported. If normality assumption is not met and the data approximately follow a log-normal distribution, data will be log-transformed before applying *t*-tests. In this case ratios of geometric means with 95% confidence intervals and *p* value will be reported. If none of the above methods hold, non-parametric methods will be considered.

Sustained microbiological eradication will be analyzed using mixed-effects models to account for the repeated measurements. Fixed effects will be the baseline microbiological eradication measured at D0, the intervention, the visit (D2 and D14), and the interaction between the intervention and the visit. Subject-specific random effect will be considered. Statistical assumptions will be assessed, and a similar methodology will be applied as for microbiological eradication to addressed them.

Primary pharmacokinetic parameters in blood (Cmax, AUC, t1/2) will be calculated for mannitol, amikacin, ceftriaxone, and for each intervention arm. In urine, descriptive statistics will be reported without any specific comparisons and spot urine concentrations.

Planned analyses will adhere to the sections detailing primary, secondary, and safety analyses, with a statistical analysis plan finalized and signed by all parties before code break. Datasets for analysis include the intention-to-treat (ITT), per-protocol (PP), and safety populations, with primary and secondary outcomes assessed in the ITT population and safety outcomes analyzed in the safety population.

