For the primary outcome, we estimated an 8% premature discontinuation before 48 h post-surgery. Complete case analysis will be performed. Sensitivity analyses considering a best–worst-case scenarios will be applied. For the secondary outcomes, missing data mechanism will be considered at random and maximum likelihood-based methods will handle the missing data providing unbiased estimates.

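### The blanket promise of unbiased likelihood estimates for secondary outcomes holds only for missing D2/D14 responses; it does not follow from the named methods when a D0 culture is missing

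*Protocol article*

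**What the plan says.** All the relevant text is in the protocol article's Statistical analysis section.

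- Missing secondary data, one sentence covering every secondary outcome: the data are taken to be missing at random, and "maximum likelihood-based methods will handle the missing data providing unbiased estimates".
- Eradication at D0 (sonicated stent culture and intraoperative urine culture, per Study endpoints): "Microbiological eradication will be compared between the same groups mentioned in the primary analysis using *t*-tests". A log transformation is the first fallback, and then: "If none of the above methods hold, non-parametric methods will be considered".
- Sustained eradication: "Sustained microbiological eradication will be analyzed using mixed-effects models to account for the repeated measurements", with D2 and D14 as the responses. The D0 value enters on the covariate side: "Fixed effects will be the baseline microbiological eradication measured at D0".

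For the primary outcome, by contrast, the plan says openly that the analysis is complete-case and adds best-case and worst-case sensitivity analyses. Secondary outcomes are assigned to the intention-to-treat population. The article does not say what happens to a patient whose D0 culture is missing.

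**The concern.** The missing-data sentence attributes a property to the secondary analyses that the methods named just before it do not all have. A two-sample t-test, its log-scale version and a rank test use only patients with an observed value. They draw nothing from the preoperative, D2 or D14 cultures, so they do not exploit a missing-at-random assumption that conditions on those cultures. In the mixed model, the ordinary likelihood given the covariates covers missing responses. A missing D0 covariate is covered only if D0 is given a model of its own, and the article names none.

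The D0 comparison is the anti-biofilm result. It answers the trial's second stated aim (Abstract), and the Discussion makes further trials depend on it. As written, it could be reported as unbiased under missing at random when it needs a stronger assumption, and no sensitivity analysis is named that would reveal the difference.

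**Working it through.** The plan states no figure to reproduce, and the sample size rests on practical considerations. The check is therefore what each named method delivers, followed by a size under stated assumptions.

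**1. Claim against method**

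| What is missing | Named method | Is the claim delivered? |
|---|---|---|
| D2 or D14 response, D0 observed | Mixed model | Yes, under missing at random and a correct model |
| D0 value, D0 comparison | Unadjusted t-test or non-parametric test | Only if missingness within arm is unrelated to the D0 count, or its relation to load is the same in each arm |
| D0 value, sustained eradication | Mixed model with D0 as covariate | Only if D0 is also modelled, or missingness is unrelated to the D2/D14 outcome given the covariates |

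**2. Patients affected.** From the document: 30 per arm, 90 in total. Assumed D0 missing rate *m*: 8% to 20%. The 8% is the plan's discontinuation figure before 48 h for the primary outcome, borrowed here only as a starting value.

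- Patients with D0 per arm, 30 × (1 − *m*): 30 × 0.92 = 27.6; 30 × 0.80 = 24.0.
- Patients without D0, of 90: 90 × 0.08 = 7.2; 90 × 0.20 = 18.

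Fitting the planned form of mixed model to simulated data on 60 patients, 10 of them without D0, used 100 of 120 rows. All 20 observed D2/D14 values of those 10 patients were left out by default.

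**3. Bias of the D0 t-test.** Assumed: two arms of 30, D0 count with SD 1.5 log10, correlation 0.5 with the preoperative count, no true effect, D0 missingness driven by the preoperative count. Two simulations were run, one with a milder dependence and one with a logistic slope of 2 per SD. Absolute bias in log10:

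| Pattern of missing D0 | Milder, 8% to 20% missing | Stronger, 8% to 20% missing |
|---|---|---|
| Random, or same dependence in both arms | about 0 | about 0 |
| Dependence in one arm only | 0.05 to 0.15 | 0.08 to 0.18 |
| Opposite directions in the two arms | 0.10 to 0.30 | 0.18 to 0.40 |

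With opposite directions, coverage of the 95% interval fell to 89% at 20% missing (milder), and from 93% to 84% over 8% to 20% missing (stronger). Every pattern in the table is missing at random given the preoperative count, which is the kind of condition under which the plan claims unbiasedness.

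**4. What removes the bias.** On the same set-up, an analysis of covariance adjusted for the preoperative count, using only patients with D0, had bias of 0.012 log10 or less. It also cut the standard error by about 10%; the large-sample limit is 1 − √(1 − 0.5²) = 13%.

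**5. Mixed model and missingness tied to later outcomes.** A large-sample simulation assumed a true D0 difference of −0.500, within-arm SD √(0.6² + 0.8²) = 1.0, and 8% of D0 missing:

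| D0 missingness depends on | t-test | Adjusted for preoperative count | Mixed-model arm effect (full data −0.240) |
|---|---|---|---|
| Preoperative count, one arm | −0.576 | −0.500 | −0.259 |
| Preoperative count, opposite by arm | −0.618 | −0.500 | −0.271 |
| Observed D2 count, both arms | −0.466 | −0.482 | −0.229 |
| Observed D2 count, one arm | −0.560 | −0.532 | −0.294 |

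The mixed-model bias is 0.02 to 0.03 in the first two rows and 0.01 to 0.05 in the last two. Adjustment for the preoperative count does not fully cure missingness related to D2.

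**The case against.** The strongest reply has five parts.

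- **Deletion is not stated.** A reader might infer that the plan drops every patient without D0. The article does not say so; it is the default of standard software. Likelihood can handle a missing covariate if that covariate is modelled, and the unseen analysis plan may do this. This stands, so the point is limited to a claim that does not follow from the methods named. It does not answer the D0 t-test, which the article does fix.
- **The sentence is right where it most naturally applies**, to missing D2 or D14 cultures. This stands.
- **Dropping patients is not bias.** A reader might infer that the D0 result will be biased. The documents do not support that: D0 samples are taken in theatre on the day of infusion, patients and assessors are blinded, and no reason is evident why cultures should go missing by load differently in each arm. This stands as to likelihood, but the plan claims unbiasedness without any such condition.
- **Keeping patients is not the remedy.** It is tempting to credit the gain to retaining patients without D0. Step 4 shows otherwise: a complete-case analysis with the preoperative count removes the bias. Likewise the standard-error inflation of 1/√(1 − *m*), 4% at 8% and 12% at 20%, reflects cultures that do not exist, and adjusting for the preoperative count does not recover them.
- **The effect is small for an exploratory pilot.** With 24 per arm the standard error of the D0 difference is 1.5 × √(2/24) = 0.43 log10, so even a bias of 0.40 is just under one standard error. This stands, and it limits the weight of the point.

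**Conclusion.** The point holds in limited form. The blanket statement is correct for missing D2 and D14 responses under missing at random and a correct model. It does not follow for a missing D0 culture, either in the D0 comparison or, unless D0 is itself modelled, in the mixed model. The D0 contrast is then unbiased only if missingness is not related to bacterial load differently by arm, nor to later outcomes.

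The size is unknown because no D0 missing rate is given. Under the assumed 8% to 20% missing, SD 1.5 log10 and correlation 0.5, t-test bias runs from about 0 (same missingness in both arms) to roughly 0.05 to 0.4 log10 (missingness tied to load differently by arm). The upper end needs strong dependence in opposite directions. The documents do not support reading this as a failed analysis or as demonstrated bias. It is a misstatement that is cheap to correct and should be corrected before code break.

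**What to change.** 1. Replace the D0 t-tests by a comparison of log10 counts between the same arms, adjusted for the preoperative urine count. Do this separately for sonicated-stent and intraoperative urine counts, which are different specimens. The preoperative count is already recorded (Data collection and management), and a preoperative culture is needed for eligibility.
2. Optionally, for urine only, model D0, D2 and D14 counts as responses in one likelihood-based repeated-measures model with arm, visit, arm-by-visit and the preoperative count as baseline covariate. A missing D0 urine culture is then a missing response, and missingness related to observed D2 or D14 counts is also covered. Stent counts should not be pooled into this model.
3. Limit the missing-data sentence to outcomes analysed by likelihood, under missing at random given the variables in the model, and say how a missing D0 value is handled.

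Cost: wording and a change of model, with no new data. The D0 contrast then relies on a simple model in place of an unadjusted test. If D0 urine becomes a response, the D2/D14 contrast is no longer conditional on D0, so the sustained-eradication comparison changes meaning and the text should say so.

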### Oversight and monitoring

In this single-center trial, monitoring will be assumed by the clinical trial unit (EB) of the CHUV. Due to its exploratory nature and limited number of participants, no interim analysis will be performed.

Full review of key data (eligibility, primary outcome, and IMP administration) for 20% of the patient’s eCRF is planned in line with Swiss Clinical Trial Organization guidelines for risk-based monitoring and ICH-GCP. In view of the limited number of patients, of the well-established substances in the intervention and a nonetheless scheduled monitoring, a DMC was not deemed necessary.

Reporting of adverse events (AEs) or serious adverse events (SAEs) will be reported to the sponsor. SAEs will be reported within a 24-h period and any lethal SAE will be communicated within 7 days to the IRB. Evidence suggests that SAEs are not anticipated due to the long-standing use of medications. AEs such as transient nephrotoxicity or ototoxicity with aminoglycoside may be anticipated but are likely to be very infrequent due to the single use of this amikacin and its favorable profile compared to other aminoglycosides. Such AEs and SAEs will be reported to the Swiss Agency for Therapeutic Products (Swissmedic) as required indicating expectedness, serious-ness, severity, and causality.

### Patient and public involvement

The importance of the topic of antibiotic resistance and its incidence in patients undergoing repeated antibiotic prophylaxis as it is in long-term stent carriers was evaluated using questionnaires addressed to this target population. Their answers clearly showed that—in addition to the fear of antibiotic-associated side effects such as diarrhea—there is great respect for antibiotic resistance and multi-resistant germs. The question posed by the study is therefore also relevant to the general population.

### Dissemination plans

Data collected during the trial will be presented in conferences in concerned fields (infectious diseases, clinical pharmacology, and urology) and will be published in peer-reviewed journals.

## Discussion

Catheter-associated infections are a growing problem in healthcare. This is mainly due to the capacity of pathogens to form biofilms on foreign material [21]. Currently, the only antibiotics displaying activity against Gram-negative biofilms are quinolones [12]. However, a single mutation in the gyrase, the quinolones’ target, suffices to decrease a pathogen’s susceptibility [22]. Consistent with this, quinolones are ineffective in over 20% of cases due to rapidly increasing resistance, posing a significant challenge [23].

The lack of new antibiotics can be partially compensated by improving existing ones. Aminoglycosides are antibiotics with excellent activity and low bacterial resistance that are hampered by dose-dependent toxic effects in patients (nephrotoxicity and ototoxicity). They can be activated against prevalent Gram-negative pathogens (*E. coli*, *K. pneumoniae*) by specific metabolites, of which mannitol is highly interesting as it has not only a great impact on biofilms but is also nephroprotective. UROPOT is a first-in-class randomized trial of metabolism-based antimicrobial potentiation. The trial will test whether boosting the activity of aminoglycosides thereby enables the effective use of less toxic drug concentrations in patients with bacterial colonization and ureteral stent manipulation. Both amikacin and mannitol are readily available and cheap. Patient safety is high as all drugs used are well established. The potential side effects are well known and manageable and patient in whom potential harm could occur are excluded. The potential clinical impact, however, is significant, as new strategies for the rise in antibiotic resistance are urgently needed. Moreover, if anti-biofilm activity is confirmed, the application of the strategy beyond prophylaxis could be considered with clinical trials for complicated stent-associated urinary tract infections or infect-associated urolithiasis as a next step.

The potentiation of existing antibiotics represents a new and promising approach to circumventing bottlenecks of antibiotics development [14]. In addition, the combination of aminoglycosides with mannitol, as used here in the UROPOT trial, has the great advantage that the oto- and nephroprotective effect of mannitol can be utilized. On the one hand, the low dosage reduces potential side effects and toxicity of aminoglycosides, and on the other hand, mannitol seems to provide additional direct protection [15]. In addition to the effect of biofilm eradication, as demonstrated in preclinical models, the combination thus represents a unique protective and effective drug interaction which is the backbone of the UROPOT trial. UROPOT is already running at the Urology Outpatient clinic of CHUV.

A potential challenge in the UROPOT trial is achieving effective concentrations of amikacin and mannitol in the urinary tract for a sufficient period. Our current schedule may not allow a sufficient exposure for maximal effect to take place. To address this issue, bacterial strains derived from patients will be characterized in biomimetics for kinetics of potentiation within our consortium ([name]). This should identify potential strains refractory to potentiation and better calibrate dosing of antibiotics and metabolites in the urinary tract.

Logistically, the UROPOT trial does not face significant challenges as a single intervention is performed with 14-day follow-up consistent with standard of care. Adherence to treatment protocols is therefore simple and additional visits are straightforward. There is limited data collection and analysis, which should also make addressing potential safety concerns associated with the investigational therapy straightforward.

## Conclusion

The UROPOT trial presents a very promising approach poised to reshape clinical practices regarding antimicrobial prophylaxis in urological procedures. The combination of mannitol and low-dose amikacin holds potential as a future standard in antimicrobial prophylaxis for endourological interventions but potentially also for applications beyond prophylaxis.

## Trial status

The current version of the protocol version 2.0, 12.12.2023. The trial started on 15.02.2024, and the expected date for recruitment will be completed is 14.02.2026. Any modification of the protocol will be submitted for approval to the local IRB (CER-VD) and the Swiss Agency for Therapeutic Products (Swissmedic).

## Data Availability

After eCRF validation by the PI, the database will be locked, saved, and extracted for analysis. Data will be extracted into several clinical trial datasets (all together forming the clinical trial database) upon format requested by the statistician. The clinical trial datasets will be stored for 10 years on electronic folders secured on the CHUV servers and protected by passwords. The database will be archived for 10 years after study end.

## Abbreviations

eCRF: Electronic case report form
ITT: Intention-to-treat
